
### Recruitment and data collection

A list of patients with heart failure who are admitted at each center will be sent to the research team daily by heart failure nurses/research coordinators from these centers. The research team will then screen the list for eligibility criteria and approach the patient and family members for participation in the study; those agreeable to participate will be administered a written informed consent form and administered the baseline survey.

Eligible patients who consent to participate in the RCT and answer the survey questionnaires will be randomized to the ACP and control arms. Participants who are randomized into the intervention (ACP) arm will meet with ACP facilitators within 48 hours of consent for intervention delivery. Patients randomized to the control arm will not take part in ACP discussions and documentation, but will continue to receive usual care.

Randomization will be done using block randomization by generating a random allocation sequence of participants to the intervention and control arms through a computerized random number generator. This will be done by a statistician at the institution. The allocation will be concealed in sequentially numbered, opaque and sealed envelopes by the data manager and given to the research coordinator conducting patient recruitment at the two centers. Envelopes will be opened sequentially by the research coordinator only after the participant unique ID is written on the envelope. Randomization sequence will not be known to the research coordinator, health care providers (physicians, ACP facilitators, heart failure nurses) and other researchers involved in the study.

Patients will be followed by the research team for 1 year or until death, whichever is earlier. Further follow-up may be needed if the targeted number of deaths in the intervention and control arms is not reached within the 1-year follow-up period. Patients will be interviewed first at baseline and then every 4 months. At the end of the follow-up period, their medical and billing records will be reviewed to assess the treatment they received and related costs. All questionnaires for both patients and caregivers will be administered in their preferred language from a selection of four: English, Mandarin, Malay, and Tamil. If the patient dies during the study, consenting caregivers will be asked to complete a post-death questionnaire (Fig. 1).

**Fig. 1 Fig1:**
[figure not shown]
Study procedures

Patient particulars and details of their next follow-up will be stored on a secure database to be built before the commencement of the study. This database will send text reminders to patients and their interviewers before every follow-up visit. Unique log-in for staff will be required for access.

### Sample size

Similar to a previous RCT, [14] we assumed that the proportion of patients receiving EOL care consistent with their stated preferences in the control arm will be 15 % compared to 65 % in the intervention arm. To achieve 90 % power to detect a difference in outcome between arms with a certainty of 95 %, we estimated that we will need 14 deaths in the intervention arm and 28 deaths in the control group. Assuming a mortality of about 15 % in 1 year, we will require at least 94 patients in the intervention arm and 188 patients in the control group. If the total number of deaths in the intervention and control arms is not reached during the planned 1-year follow-up period, further follow-ups will be needed.

### Proposed statistical analysis

All analysis will be done as per the intention-to-treat principle. In addition, a “per-protocol” analysis will also be conducted. For the analysis of primary outcome, we will use the kappa statistic to assess congruence between preferred and actual place of death and for each of the life-sustaining treatments. The chi-square test or Fisher’s exact test as appropriate will be used for testing the association between receiving care consistent with patients stated preference and the type of intervention. The analysis will be conducted in the sub-group of patients who die during the study duration.

For comparing health care expenditures between the two arms, we will use ordinary least squares regression to model health care expenditures with the type of intervention as the primary predictor. The model will adjust for any differences in baseline characteristics between the two arms and primary diagnosis. If health care expenditure data are not normally distributed, appropriate transformations or two-part models will be used.

For comparing quality of life, anxiety and depression, understanding of own illness and participation in decision-making, we will use separate mixed-effects models to analyze the changes over time and determine if change over time differs between the intervention and control arms. We will adjust for differences in baseline characteristics between the intervention and control arms in the model. Missing observations will be accounted for under the missing-at-random assumption of the mixed-effects model. This is a reasonable and common assumption. If the data are not normally distributed, appropriate transformations will be attempted before resorting to the use of nonparametric statistical analysis methods. Finally, the kappa statistic will be used to test the congruence between the patient’s preference and the caregiver’s preference in the analysis of the secondary outcome.

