### Outcome measures

#### Primary outcome

The primary outcome to be assessed in the study is the proportion of patients receiving EOL care consistent with their stated preferences. Patients’ stated preferences for CPR, life-prolonging treatments (comfort measures only/limited intervention/full treatment), place of care and place of death will be assessed from their last survey or their ACP document. The actual treatment received by the patient will be assessed from their medical records after the patient’s death. If these records are unavailable, this information will be assessed in post-death interviews with the patient’s family members/surrogate decision-maker. Actual place of death will be ascertained from death certificates and actual place of care from post-death interviews with the patient’s family members/surrogate decision-maker. The analysis will only be conducted for the sub-group of patients who die during the study period.

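### Kappa is a poor index of per-item concordance and the only named measure of patient-caregiver congruence; proportions concordant by arm should be reported, with kappa kept as descriptive

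*Protocol article*

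**What the plan says.** The Primary outcome section sets the target as "the proportion of patients receiving EOL care consistent with their stated preferences". The items are listed there: "Patients’ stated preferences for CPR, life-prolonging treatments (comfort measures only/limited intervention/full treatment), place of care and place of death will be assessed".

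The Proposed statistical analysis section names two tools for this outcome. The first is per item: "we will use the kappa statistic to assess congruence between preferred and actual place of death and for each of the life-sustaining treatments". The second is the chi-square or Fisher's exact test, which "will be used for testing the association between receiving care consistent with patients stated preference and the type of intervention". Both apply to decedents only: "The analysis will be conducted in the sub-group of patients who die during the study duration". The Sample size section plans for "14 deaths in the intervention arm and 28 deaths in the control group".

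For the secondary outcome of patient-caregiver agreement, one measure is named: "the kappa statistic will be used to test the congruence between the patient’s preference and the caregiver’s preference". The Background hypothesises that this congruence will be greater under ACP, which is a statement about a difference between arms.

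**The concern.** Kappa measures agreement beyond what the margins would produce by chance. It does not measure how many patients got what they wanted. When the margins are very uneven, chance agreement is high and kappa can be near zero although almost everyone's care matched. With as few as 14 deaths in an arm, an empty row or column is a realistic event.

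The intervention makes this relevant to a comparison of arms. According to the Intervention section, ACP elicits, documents and updates preferences and brings the family into the discussion. It may therefore move the margins in one arm and not in the other. Two kappas set side by side would then differ partly because the margins differ. A reader could take a low or missing ACP kappa as poor congruence when more ACP patients received matching care. The per-item kappas could also appear to contradict the chi-square/Fisher result on the same patients.

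The exposure is greater for patient-caregiver congruence. No other measure is named, and the hypothesis about the arms can be addressed only by reading kappa across them.

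**Working it through.** **Planned size.** Inputs from the Sample size section: 65% v 15%, 90% power, 95% certainty (two-sided 5% assumed); allocation 1:2. Using the pooled-variance formula without continuity correction:

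- Pooled proportion = (0.65 + 2 × 0.15)/3 = 0.3167.
- n(ACP) = [1.960 × √(1.5 × 0.3167 × 0.6833) + 1.282 × √(0.65 × 0.35 + 0.15 × 0.85/2)]² / 0.50² = (1.117 + 0.692)² / 0.25 = 13.1, so 14, with 28 controls.
- Patients: 14/0.15 = 93.3, so 94, and 2 × 94 = 188.

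The article's figures reproduce and are not in dispute. They fix the size of the kappa tables at 14 and 28.

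**Kappa.** κ = (po − pe)/(1 − pe), where po is observed agreement and pe is the agreement expected from the margins. The cell counts below are illustrations; the article gives no preference or treatment distributions.

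| Arm and table (CPR) | po | pe | κ |
|---|---|---|---|
| ACP, n = 14: 13 refuse, 1 wants it, none receives it | 13/14 = 92.9% | 92.9% | 0.00 |
| ACP, n = 14: all refuse, none receives it | 100% | 100% | 0/0, undefined |
| ACP, n = 14: 13 refuse and do not receive, 1 wants and receives | 100% | 86.7% | 1.00 |
| Control, n = 28: 8 wanted and received, 6 wanted and did not, 4 refused and received, 10 refused and did not | 18/28 = 64.3% | 50.0% | 0.29 |

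The first row is general. If one margin is constant, po equals pe and κ is 0, or 0/0 when everyone falls in one concordant cell. A three-level item with the same pattern also gives 0.

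**The same data as proportions.** 13/14 v 18/28: Fisher p = 0.067. 14/14 v 18/28: Fisher p = 0.017. In both, the arm with more matching care is shown as higher.

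**Chance of an empty margin.** If a share r of decedents receives CPR (assumed), the chance that none of 14 does is (1 − r)^14: 49% for r = 5%, 23% for 10%, 10% for 15%.

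**How often the order is lost.** Trials with 14 and 28 deaths were simulated for CPR. The table shows, among trials with higher ACP agreement, the share in which ACP kappa does not exceed control kappa. An undefined kappa counts as not exceeding. Base assumptions: refusal followed in 95% (ACP) and 85% (control); CPR given to 40% of those who want it, in both arms.

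| Wanting CPR, ACP v control | Share |
|---|---|
| 10% v 50% | 58% (46% if undefined values are left out of the count) |
| 20% v 50% | 37% |
| 30% v 50% | 24% |
| 50% v 50% | 8% |
| 10% v 50%, wish for CPR met in 80% under ACP | 32% |
| 20% v 50%, wish for CPR met in 80% under ACP | 11% |

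In the first scenario mean agreement is 89% v 63%, and ACP kappa is at or below 0 or undefined in 57% of all trials. If the overall planning rates of 65% v 15% are instead applied to a single item (an assumption), the share is under 1% for every preference mix tried: 10% v 50%, 20% v 50%, 30% v 30% and 50% v 50%.

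**Patient-caregiver pairs.** With 94 pairs per arm (illustration only), 70/94 = 74% agreement with even margins gives pe = 0.50 and κ = 0.49. Agreement of 86/94 = 91% with about 95% refusing on both sides gives pe = 0.90 and κ = 0.16.

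**The case against.** The strongest reply is that the trial's main inference does not use kappa. The between-arm question goes to a chi-square or Fisher's exact test on consistent care, which is a comparison of proportions. No sentence says that the per-item kappas will be compared between arms. This stands: a reader might infer that the primary comparison is distorted, and the article does not support that.

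Second, kappa can be informative where raw agreement is not. In the 13-of-14 example, the one patient who wanted CPR did not receive it, so care did not vary with preference. Kappa of 0 shows this, while 93% agreement hides it. This also stands, and it is a reason to keep kappa and the two-way table beside the proportion.

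Third, the frequencies depend on chosen inputs, only CPR was modelled among the treatment items, and at the planning rates reversal is rare. This limits the size of the claim but not the algebra.

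Fourth, a condensed article may leave reporting detail to a fuller document. That covers interval methods and table layouts. It does not cover the choice of statistic, which the article states for both outcomes.

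**Conclusion.** The point holds as a cheap improvement. Kappa per item does not measure the proportion that the article defines as its outcome. It is also the only measure named for a secondary outcome on which a difference between arms is hypothesised. At the planned numbers of deaths, 93% agreement can score 0.00 against 0.29 for 64%, and complete agreement in one category yields no value.

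Two stronger readings are tempting and wrong. An arm with 100% agreement cannot score below one with 64%, because its kappa is either undefined or 1. Nor is it enough that nearly all patients prefer and receive the same thing: 13 matching in one category plus 1 matching in the other gives kappa 1. A value of 0 is forced only when preference or care received is constant within the arm.

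How often kappas read across arms would mislead cannot be settled from the article. The range of about 8% to 58% rests on assumed CPR preferences and treatment rates, and the top figure counts undefined values. Under the planning rates applied to an item it is below 1%. The primary chi-square/Fisher comparison is unaffected in all of these.

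**What to change.** In Proposed statistical analysis, state that for each end-of-life item, and for patient-caregiver pairs, the proportion concordant will be reported in each arm with a 95% CI, together with the arm difference, tested by chi-square or Fisher's exact test. Show the preferred-by-received table, or the patient-by-caregiver table, for each arm. Keep kappa as a descriptive measure and state that it will not be compared between arms.

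This changes wording only and needs no new data. The downside is that raw agreement is not corrected for chance, which is why the two-way tables and kappa should stay beside it.

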Despite the promise and popularity, there has been little research evaluating the effectiveness of ACP in meeting patient preferences, especially in Asian settings. One randomized controlled trial (RCT) of the “Respecting Choices” model for ACP, among elderly hospitalized patients in Australia, has reported positive outcomes in enabling people to receive EOL treatment as per their wishes [14]. Another controlled trial, conducted in a nursing home in the US also found higher compliance with patients’ wishes among those receiving ACP [15]. An RCT by Kirchhoff et al. [16] among individuals with CHF or end-stage renal disease failed to show any significant difference in the proportion of patients who met their preferences regarding cardiopulmonary resuscitation (CPR) between the ACP and control arms. Thus, there has been mixed evidence regarding the effectiveness of ACP, with none from an Asian setting.

This study aims to fill this gap. It is a two-arm RCT of patients with advanced CHF to assess the impact of ACP on health and cost outcomes. The study will be conducted in Singapore, a rapidly aging country in Southeast Asia. We will survey the patients in both arms every 4 months for a period of 1 year or until they die, whichever is earlier. The primary objective of this trial is to assess whether patients receiving ACP have a greater likelihood of receiving EOL care consistent with their preferences compared to patients receiving usual care. Secondary objectives are to compare heath care expenditures, quality of life, anxiety and depression, understanding of own illness, participation in decision-making and concordance with caregiver preferences for EOL care between patients receiving ACP and usual care. We hypothesize that patients receiving ACP will be more likely to receive EOL care consistent with their stated preferences, and have lower health care expenditures, better quality of life, lower anxiety and depression, better understanding of their own illness, greater participation in decision-making, and greater congruence with caregiver preferences, as compared to patients receiving usual care.

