## Methods/design

### Study design

This is a two-arm RCT of ACP versus usual care conducted at two institutions in Singapore –the National Heart Centre Singapore and Singapore General Hospital (Department of Internal Medicine). The two hospitals were chosen because they are the largest centers/hospitals that currently have trained ACP facilitators to deliver ACP to patients with advanced CHF. All ACP facilitators in Singapore are trained based on similar principles and with similar intensity and methodology. Therefore, the study results are likely to be generalizable to patients with advanced CHF who are receiving ACP at any hospital in Singapore.

Two hundred and eighty-two in-patients with advanced CHF (*n* = 94 in the ACP arm; *n* = 188 in the control arm receiving usual care) will be recruited from these centers and followed for 1 year or until they die, whichever is earlier. Additionally, the study will include up to one caregiver per patient enrolled.

Randomization will follow a 1:2 (ACP: control arm) ratio. The unequal number of patients in the ACP and control arms is because it was anticipated that over the course of the study duration, due to increasing popularity of ACP in Singapore, many patients in the control arm may decide to take up ACP, thus contaminating the control arm. If this happens, the larger number of participants in the control group is expected to increase the statistical power for a “per-protocol” analysis [17].

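### The expenditure comparison guards against non-normal costs but not unequal spread; at 94 v 188 patients, a pooled OLS standard error is modestly off if cost variances differ between arms

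*Protocol article*

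**What the plan says.** All references are to the protocol article.

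- Proposed statistical analysis, on costs: "we will use ordinary least squares regression to model health care expenditures with the type of intervention as the primary predictor". Covariates follow: "The model will adjust for any differences in baseline characteristics between the two arms and primary diagnosis".
- The one contingency in the same paragraph: "If health care expenditure data are not normally distributed, appropriate transformations or two-part models will be used". It depends on the shape of the distribution, not on whether the arms have equal variance.
- Study design: "Randomization will follow a 1:2 (ACP: control arm) ratio". Sample size: "we will require at least 94 patients in the intervention arm and 188 patients in the control group".
- Background: the trial expects ACP patients to "have lower health care expenditures". This concerns the level of cost; nothing is said about its spread.

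The article does not say whether the OLS standard error is classical (pooled) or robust. It gives no SD, effect size or power for expenditures, which is the first secondary outcome listed.

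**The concern.** The classical OLS standard error uses one residual variance for both arms. With equal arms, unequal variances cancel: the pooled formula gives (s_A² + s_C²)/n, which is also the true variance of the difference. With 1:2 allocation they do not cancel, because the pooled variance is weighted towards the larger arm while the true variance of the difference depends more on the smaller one.

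Cost data often have a spread that rises with the mean. If that holds here and ACP lowers costs, the smaller arm has the smaller variance and the pooled standard error is too large. If ACP costs are more variable, for example through a few very expensive patients, it is too small. At these sample sizes normality, which the plan checks, matters less for a difference in means than equal variance, which it does not. At stake are the width of the cost interval and some power, not the point estimate.

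**Working it through.** **Design figures.** Rates of 65% v 15%, 90% power, two-sided 5% and ratio 1:2 give, by the usual two-proportion formula without continuity correction, 13.08, rounded up to 14 deaths under ACP and hence 28 under control. Then 14/0.15 = 93.3, rounded up to 94, and 2 × 94 = 188. The arm sizes reproduce. They rest on the primary outcome alone.

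**Inputs for the cost check.** n_A = 94 and n_C = 188, from the article. r = SD under ACP / SD under control: an assumption, varied below. No covariates; control variance set to 1.

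**Formulas.**
- True variance: V = r²/94 + 1/188
- Pooled OLS variance: V_OLS = [(93r² + 187)/280] × (1/94 + 1/188)
- Error factor: k = √(V_OLS/V)

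**Worked cases.** 1/94 + 1/188 = 0.015957.
- r = 0.8: V_OLS = (246.52/280) × 0.015957 = 0.014049; V = 0.012128; k = √1.158 = 1.076. Sample effectively lost: 1 − 1/1.158 = 13.7%.
- r = 0.7: V_OLS = (232.57/280) × 0.015957 = 0.013254; V = 0.010532; k = √1.258 = 1.122. Sample effectively lost: 1 − 1/1.258 = 20.5%.
- r = 1.25: V_OLS = (332.31/280) × 0.015957 = 0.018939; V = 0.021941; k = √0.863 = 0.929.

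| r | OLS SE / true SE | Coverage of nominal 95% interval | Power where a correct SE gives 80% |
|---|---|---|---|
| 1.0 | 1.000 | 95.0% | 80% |
| 0.9 | 1.036 | 95.8% | 78% |
| 0.8 | 1.076 | 96.5% | 76% |
| 0.7 | 1.122 | 97.2% | 73% |
| 0.6 | 1.172 | 97.8% | 69% |
| 1.25 | 0.929 | 93.1% | not comparable (interval too narrow) |

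Coverage and power use the normal approximation.

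**Simulation on the raw scale** (20,000 trials per scenario, SD proportional to the mean):
- Lognormal, CV 1.0, 20% saving: power 40.9% with pooled OLS v 47.7% with unequal variances; coverage 96.6% v 95.3%.
- Gamma, CV 1.0, 20% saving: power 39% with OLS v 45% with HC3.
- Gamma, ACP costs 30–50% higher: OLS coverage about 91–93%, HC3 about 94–95%.
- Lognormal, identical distributions: OLS rejects in 4.4–4.8%.

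**Does a log scale remove it?** If ACP multiplies every cost by one factor, log-cost variance is equal in both arms and k = 1. If the saving falls on the costly tail, it is not. Assume lognormal costs, control CV 1.5 and equal medians. Control log-variance is ln(1 + 1.5²) = 1.179.
- ACP mean 20% lower: log-variance 1.179 + 2 ln 0.8 = 0.732; r² = 0.621; k = 1.08.
- ACP mean 30% lower: log-variance 1.179 + 2 ln 0.7 = 0.465; r² = 0.395; k = 1.16.

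In this pattern the log-scale arm effect is zero, because the medians are equal, although mean cost differs by 20% or 30%. The log model is answering another question.

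**The case against.** Three objections carry weight.

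1. Skewed costs of the kind simulated would almost certainly fail a normality check, so the article's own clause would move the analysis off the raw scale. Under the very assumption that gives the 8% and 12% figures (SD proportional to the mean), log-scale OLS with the ordinary standard error is correct: simulated coverage is about 95%. This stands. A reader might infer that the problem persists under any transformation; it does not. The clause is still not a full safeguard. It leaves the choice open, a log scale protects only against a proportional effect, and it gives up the difference in mean expenditure.

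2. OLS is an estimator and is compatible with robust standard errors. The article does not commit to the pooled one, and a journal protocol may leave that to a fuller document. This stands too: no error or contradiction has been shown. What remains is that the article does state a contingency, and it addresses shape rather than spread.

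3. A reader might infer that the trial's own hypothesis makes the intervals wrong. The Background predicts a lower mean only. The link from mean to spread, the CV and the size of the saving are all assumptions, and the sign reverses if ACP costs are more variable.

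**Conclusion.** The point holds in conditional form and is minor. If costs are analysed by OLS with the pooled standard error and the arms differ in spread, 1:2 allocation makes the interval for the arm effect miss its nominal coverage. On the raw scale, with SD proportional to the mean and ACP costs 20–30% lower, it is about 8–12% too wide. That error is conservative, costing roughly 4 to 7 points from a nominal 80% power, and false positives are not inflated. With an SD ratio of 1.25 in the other direction it is about 7% too narrow. If the cost distributions are the same, nothing is lost. The figures ignore covariates, and every SD ratio is assumed because the article reports no cost SD. The outcome is secondary and has no stated power, so this is a low-cost improvement and not a demonstrated fault.

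**What to change.** Add one sentence to the expenditure paragraph of Proposed statistical analysis: for any OLS cost comparison, whether on the raw scale, on a transformed scale or for the positive-cost part of a two-part model, the confidence interval and p-value for the arm effect will use HC3 standard errors, or a bootstrap that resamples patients within arm. The point estimate does not change. With arm as the only regressor, HC3 gives s_A²/93 + s_C²/187, so each arm contributes its own variance.

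The cost is one software option. The downside is a wider interval than pooled OLS if the ACP arm proves more variable, which is then the appropriate width. Under equal spread practically nothing is lost. The change does not restore the mean cost difference if a log scale is chosen; that remains a separate choice of estimand.

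### Secondary models choose covariates by observed baseline imbalance and the cost model by a normality check; covariates, cost target and cost estimator should be fixed in advance

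*Protocol article*

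**What the plan says.** All the relevant rules stand in the protocol article under Proposed statistical analysis.

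- Cost model, default: "we will use ordinary least squares regression to model health care expenditures with the type of intervention as the primary predictor".
- Cost model, covariates: "The model will adjust for any differences in baseline characteristics between the two arms and primary diagnosis". Primary diagnosis is the only covariate named, and it is not defined.
- Cost model, fallback: "If health care expenditure data are not normally distributed, appropriate transformations or two-part models will be used". The article gives no criterion for non-normality, no choice between the two options and no quantity to be compared.
- Mixed-effects models for quality of life, anxiety and depression, understanding of illness and decision-making: "We will adjust for differences in baseline characteristics between the intervention and control arms in the model". No covariate is named.

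The Background gives the cost hypothesis only in general terms, that patients receiving ACP will "have lower health care expenditures, better quality of life, lower anxiety and depression". The scale on which costs should be lower is not stated. On allocation: "Randomization will follow a 1:2 (ACP: control arm) ratio" and "Randomization will be done using block randomization by generating a random allocation sequence".

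**The concern.** Two data-dependent choices are written into the plan.

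**Covariates.** With concealed block randomisation, baseline differences between arms arise by chance. Whether a variable differs says nothing about whether it predicts the outcome. A rule driven by imbalance usually leaves out the variables that would sharpen the comparison. Because no threshold and no list are given, it also allows adjustment to be chosen once data are in hand, in a trial that the Limitations section says cannot be double-blinded.

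**Cost scale.** Least squares on raw costs compares arithmetic means. A log transformation compares geometric means unless the result is converted back. If the normality check decides which is reported, it can also decide what the cost result means.

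At stake are the precision of the secondary comparisons, above all costs, and the interpretation of the cost result.

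**Working it through.** **1. The plan's own figure.** None is given for the secondary models; the only design figure concerns the primary outcome. Inputs from the Sample size section: 65% vs 15%, 90% power, 5% level (taken as two-sided), allocation 1:2. The pooled formula without continuity correction, with average proportion (0.65 + 2×0.15)/3 = 0.317, gives for the ACP arm

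[1.96·√(1.5×0.317×0.683) + 1.282·√(0.65×0.35 + 0.15×0.85/2)]² / 0.50² ≈ 13.1, so 14 deaths, and 28 in control.

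Dividing by 15% mortality: 14/0.15 = 93.3 and 28/0.15 = 186.7, hence 94 and 188 with the ratio kept. The figure reproduces. Neither issue here touches it; 94 and 188 are used below.

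**2. Precision under the covariate rule.** In outcome-SD units, the unadjusted standard error is √(1/94 + 1/188) = 0.126. With a prognostic covariate always included it is 0.126×√(1 − R²). If the covariate enters only when it differs at p<0.05, it enters in about 5% of trials, so the standard error stays close to 0.126. Simulation (10,000 trials per row, one prognostic covariate, no treatment effect; R² and the p<0.05 trigger are assumptions):

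| R² | SE, imbalance rule | SE, prespecified | SE larger by | Effective sample kept | Type I error, rule |
|---|---|---|---|---|---|
| 0.10 | 0.126 | 0.120 | 5% | 91% | 4.9% |
| 0.25 | 0.125 | 0.110 | 15% | 76% | 4.1% |
| 0.40 | 0.125 | 0.098 | 28% | 61% | 4.2% |
| 0.50 | 0.125 | 0.089 | 39% | 51% | 3.7% |

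Effective sample kept is the squared ratio of the two standard errors, before rounding. These are model standard errors. The actual spread of the estimates differs a little less: 0.1252/0.1205, 0.1208/0.1081, 0.1193/0.0979 and 0.1182/0.0896, or 4%, 12%, 22% and 32% larger. The reported standard error exceeds the true spread, which is why the test is conservative.

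**3. Will the cost fallback be used?** Lognormal costs at n = 282 failed a Shapiro-Wilk test in 99.9% of runs with log-SD 0.3 and in all runs with 0.5 and 1.0 (1,000 runs each). For inpatient bills the fallback is effectively the planned analysis.

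**4. What a log model can change.** For lognormal costs, arithmetic mean = geometric mean × exp(log-SD²/2), so

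arithmetic ratio = geometric ratio × exp[(s²_ACP − s²_control)/2].

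- Log-SD 1.2 control, 1.0 ACP: the factor is exp(−0.22) = 0.80. A geometric ratio of 1.15 (ACP dearer) is an arithmetic ratio of 0.92 (ACP cheaper).
- Log-SD 1.0 control, 1.2 ACP: the factor is exp(0.22) = 1.25. A geometric ratio of 0.90 is an arithmetic ratio of 1.12.

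Rejection rate of a 5% log-scale test when the arithmetic means are equal (simulated at 188 and 94):

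- equal log-SDs: about 5%
- 1.0 vs 1.1: 11–13%
- 1.0 vs 1.2: 31–38%, against 4–7% for an unequal-variance test on raw costs

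Hand check of the last case (1.0 control, 1.2 ACP): the log-scale shift is 0.22, its standard error √(1/188 + 1.44/94) = 0.144, the ratio 1.53, and the chance of passing 1.96 about 33%.

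**The case against.** The strongest reply has five parts.

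- **The precision loss depends on assumptions.** The article gives no R², no threshold and no list of variables. At R² = 0.10 the loss is 5%, and a looser trigger would admit more covariates and lose less. The mixed-effects models analyse change on scales measured at baseline, so they already use much of the baseline score. This stands: the table describes the cost model, and the loss in the mixed models is smaller.
- **No false positives follow from the rule.** A reader might infer that selecting covariates after looking inflates type I error. Applied mechanically, it does not: the rate is 3.7–4.9%. What remains is lost precision and room for discretion.
- **The cost fallback need not change the target.** A two-part model, or a transformed model converted back, can estimate arithmetic mean cost. If ACP has no effect on costs at all, the two distributions are the same and the log test is valid. With equal spread and a true 30% reduction, the log test is more powerful than the raw-scale test (82% vs 67% at log-SD 1.0; 65% vs 49% at 1.2). This stands: the meaning can change but need not.
- **No stated objective is breached.** It is tempting to say that the plan departs from an objective of mean expenditure. The article states no such target; the fair criticism is that the target is undefined.
- **Primary diagnosis may be useful.** One might infer that it hardly varies because everyone has advanced heart failure. The term is undefined and could mean admission diagnosis or cause of heart failure, so the article does not support dropping it. It is also the one covariate fixed in advance.

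The reply that such details belong in an unseen analysis plan does not succeed. The article states the imbalance rule twice and states the normality switch; an analysis plan could only follow these rules or contradict them.

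**Conclusion.** The point holds as a poorly chosen stated method for the secondary outcomes. Covariate choice by observed imbalance costs roughly 5% to 39% in the cost model's standard error over R² of 0.10 to 0.50, if the trigger is p<0.05. It costs less in the mixed-effects models, and it leaves adjustment open to choice in an unblinded trial. The normality switch will almost certainly be triggered for costs, and the comparison it leads to is not defined. A log model without retransformation misleads about mean cost only if spread differs between arms: negligibly when log-SDs are equal, seriously at 1.0 vs 1.2. The R² values, the trigger and the log-SDs are assumptions, since the article gives none.

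The primary chi-square or Fisher test and the sample size are not affected. The change should be made, but the trial's main conclusion does not depend on it.

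**What to change.** - **Covariates.** Replace both adjustment sentences with one rule: adjust for site, age and NYHA class whatever the observed imbalance. For KCCQ, HADS and the Decisional Conflict Scale, use the baseline score either as a covariate or as a response in the mixed model, not both. Primary diagnosis may stay in the cost model once defined. Expenditure is measured over the study and has no stated baseline counterpart, so none is proposed.
- **Costs.** State the difference in arithmetic mean inpatient cost as the target. Fix one estimator whatever a normality check shows, for example least squares with a bootstrap confidence interval, or a gamma model with log link and robust standard errors with the mean difference derived from it. Log-scale results may be reported as supportive.

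The cost is a change of wording. NYHA class and age are needed for eligibility, site is known, and the three scales are administered at baseline. Recruitment and data collection do not change. The small downside is some loss of power for costs, relative to a log-scale test, when spread is equal in the two arms.
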